### Randomisation

Participants who are eligible will be randomly assigned by the research team following simple randomisation procedures (computerized random numbers using Excel random number generator feature) to either G4H or CBT using a 1:1 ratio. Participants will be randomised at the group level once sufficient participants have been recruited for a group (minimum of 5). That is, participants will first be recruited into a treatment group, and each group will then be randomised to receive either G4H or CBT, using the randomisation process outlined above. Neither the participant nor the research team will be blind to intervention status. Assessment of primary outcomes at each timepoint will occur via a web interface to ensure that this is not affected by intervention status.

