### Sample size power calculations

The CARR sample size was determined by power calculations for a non-inferiority trial, using effect sizes and retention rates from our published pilot study. We have estimated the non-inferiority margin based on historical evidence for the effect size of the active comparator (based on recommendations by [46] and [47]). The effect size of this CBT program versus control was *d* = 0.49 at 6 month follow up (recalculated from [28] using methods recommended by [19]). This corresponds to 2.2 points on the DASS-21 depression subscale (using the expected standard deviation for an adolescent population of 4.53; [31]). To have 0.80 power to detect this difference with an alpha level of 0.05*,* 67 people per condition would need to be retained at follow up. Assuming 50% eligibility and 67% survival rates, which are consistent with our pilot data, we anticipate that screening 400 people for eligibility (see Fig. 2) will lead to retention of *N* = 67 per condition at follow up [48]. However, this is a conservative estimate of retention due to the addition of incentives for follow up data completion in this trial [49].

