### Analyses

Data quality will be improved by using a web interface that prompts (but does not force) participants to complete missing items. This will reduce missing data and prevent errors from manual data entry. Data quality will be checked by assessing ranges for each variable and interrogating outliers. We will examine the differences in baseline characteristics between the groups descriptively. Since differences between randomised groups at baseline could have occurred by chance, no formal significance testing will be conducted (in accordance with recommendations by [50]). No covariates will be included in the primary analysis (in accordance with recommendations by [51]). However, we will include exploratory analyses which assess the interaction between condition and baseline characteristics where indicated.

To assess the effect of intervention, group differences on the primary and secondary outcome measures, with all available timepoints included in the model, will be examined using a series of mixed effects repeated measures (MMRM) models, which will specify timepoint, participant, and therapy group as levels in the analyses. MMRM is a full information maximisation likelihood estimation strategy that can model data even when some observations are missing, and thus honours the intention-to-treat principle [52]. For all hypothesis testing, both intention-to-treat analyses (ITT; where all available data are included in MMRM) and per protocol analyses (PP; only including participants who met eligibility criteria throughout the trial period, were randomly assigned, completed the intervention according to the protocol, and had both baseline and follow up data) will be completed. Best fit, as determined by Information Criteria (e.g. AIC; BIC) method will be used for determining the covariance structure for MMRM models.

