H1 will be considered supported if there is evidence of significant improvements in loneliness in the G4H condition (H1a), and a significant condition by time interaction, such that improvements in loneliness over time will be greater for the G4H condition than in the CBT condition (H1b). H2 will be considered supported if there is evidence of significant improvements in depression in both conditions, with a non-significant condition by time interaction. The non-inferiority margin will be a DASS-21 depression change score difference of 2.20. H3 will be considered supported if there is no significant increase in depression and loneliness scores between T6 and T7 in the G4H condition.

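### The interaction test for H1b needs therapy-group variation in change in its error term, and the Analyses section does not secure it

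*Protocol article*

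**What the plan says.** Under Randomisation, people are first recruited into a therapy group and "each group will then be randomised to receive either G4H or CBT". The Intervention section sets group size at 5 to 9. The therapy group is therefore the randomised unit.

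Under Analyses, primary and secondary outcomes go into mixed models over all available time points, "which will specify timepoint, participant, and therapy group as levels in the analyses". The same section adds: "Best fit, as determined by Information Criteria (e.g. AIC; BIC) method will be used for determining the covariance structure for MMRM models". It does not say whether therapy group enters as an intercept only or may also vary over time.

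The decision rules follow. H1b requires "a significant condition by time interaction, such that improvements in loneliness over time will be greater for the G4H condition than in the CBT condition". H2 counts as supported when depression improves in both conditions and the interaction is not significant. A non-inferiority margin of 2.20 on the DASS-21 depression change score is also stated, without an interval procedure.

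**The concern.** Naming therapy group as a level suggests that clustering is handled. For a comparison of mean levels it may be. H1b, however, rests on a comparison of change. A group intercept applies equally at T0 and at every later time, so it drops out of that comparison.

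What remains is whether some groups change more than others for reasons unrelated to condition. The article gives grounds to expect this:

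- T0 precedes the intervention, so influences of facilitators and group climate can show only as differences in change.
- The Background reports that pilot participants whose identification with their G4H group rose were among those most likely to improve.
- Group cohesion and identification are process measures.
- Each group is run by two facilitators.

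If this variation is missing from the error term, H1b can be declared because a few groups in one arm went well. The same omission narrows any interval for the depression difference.

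**Working it through.** **The plan's own figure.** Inputs from Sample size power calculations: difference 2.2, SD 4.53, power 0.80, alpha 0.05 ("To have 0.80 power to detect this difference with an alpha level of 0.05"). Two-sided: n = 2 × (1.960 + 0.842)² × 4.53² / 2.2² = 66.6, so 67 per arm, as stated. (One-sided 0.05 would give 53.) Recruitment agrees: 400 × 0.50 × 0.67 / 2 = 67. The calculation has no clustering term, so it supplies no ICC for what follows.

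**Why the intercept cancels.** Write a score as fixed effects + b (group) + a (participant) + e. In T5 minus T0, both b and a vanish. If groups also differ in change, the change score contains g (group) + e′ with ICC ρ = var(g) / [var(g) + var(e′)]. With m analysed per group, the true variance of the arm difference exceeds the model's by DE = 1 + (m − 1)ρ. The null rejection rate of a two-sided 5% test is then 2 × [1 − Φ(1.96/√DE)].

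**Inputs.** Group size 5-9 (Intervention); midpoint 7 is assumed, so 200/7 is about 28 groups. At 67% retention m = 0.67 × 7 = 4.7. The ICC is an assumption and is shown as a range.

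| ICC of change | DE, m = 4.7 | Error | DE, m = 7 | Error |
|---|---|---|---|---|
| 0 | 1.000 | 5.0% | 1.00 | 5.0% |
| 0.02 | 1.074 | 5.9% | 1.12 | 6.4% |
| 0.05 | 1.185 | 7.2% | 1.30 | 8.6% |
| 0.10 | 1.370 | 9.4% | 1.60 | 12.1% |
| 0.15 | 1.555 | 11.6% | 1.90 | 15.5% |

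For ICC 0.05, 0.10 and 0.15, m = 5 gives 7.4%, 9.8% and 12.1%; m = 9 gives 9.8%, 14.4% and 18.6%.

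**Simulation under no condition effect** (2,000 runs per setting, 28 groups of 5-9; Monte Carlo SE near 10% is √(0.1 × 0.9/2000) = 0.7 points).

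- No group variation in change in the model: 8.15%, 9.75% and 12.75% at 67% retention for ICC 0.05, 0.10 and 0.15; 8.15%, 13.45% and 14.95% at full retention.
- Omnibus interaction over four time points, random intercepts only, group deviation persisting after T0: 8.6%, 11.8% and 15.6%. (Redrawing the deviation at every time point gives more, 10.5%, 18.8% and 25.0%, but that places it at T0 too, before therapy; it is not used here.)
- Group term offered to AIC or BIC, ICC 0.02-0.15: about 5-7% under AIC and 6-9% under BIC. At full retention AIC kept the term in 35% of runs at ICC 0.05 and 69% at 0.10; BIC kept it in 11% and 38%.
- Group term always in the model, with 28 − 2 = 26 df: 3.4-5.1% over ICC 0-0.15.

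**Interval against 2.20.** The interval is too narrow by the factor √DE. At planned retention √1.185 = 1.09 and √1.555 = 1.25, so for ICC 0.05-0.15 it should be 9-25% wider. A one-sided 2.5% error would become half the tabulated rate: 3.6% to 5.8%.

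**The case against.** The strongest reply is that the fault is inferred. The article names the randomised unit as a level and does not exclude a group-by-time term. Random-effects structure, REML and degrees of freedom are commonly left to an analysis plan, and one may exist that is not shown. The AIC/BIC sentence can also be read as covering only the within-participant structure. All of this stands, and it makes the inflation conditional. It does not remove the point: the article fixes a decision rule based on change and a fit-based rule for the covariance, and nothing in it keeps the one component that group randomisation requires for that rule.

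A reader might infer more: that the plan as written rejects 9-15% of the time for both H1 and H2, with AIC/BIC as the cause. The document does not support that.

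- The 9-15% range needs an intercept-only group term, full retention and an ICC the article does not give.
- If AIC/BIC may choose the group term, the rate is about 5-9%.
- Part of the size depends on the covariance chosen. At ICC 0.10 and full retention, a separate run gave 14.4% with compound symmetry forced and 12.6% with the unrestricted variance of change.
- H2 is supported by a non-significant interaction, so excess rejection makes it harder to claim. The harm to non-inferiority arises only through an interval, and the article describes none.

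**Conclusion.** The point holds conditionally, mainly for H1b. If therapy-group variation in change is absent from the model, the nominal 5% test runs at roughly 7-12% at the planned retention and 9-15% at full retention, for assumed ICCs of 0.05-0.15 and about seven recruited per group. Inflation is small at ICC 0.02 and nil at 0. Leaving the term to AIC/BIC reduces the problem without removing it. For H2 there are two separate effects: the literal rule becomes harder to satisfy, and an interval compared with 2.20 would be too narrow. This should be corrected before analysis; it is not evidence that the trial will reach a false conclusion.

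**What to change.** In the Analyses section, or in the analysis plan with a reference from it:

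1. State that the primary model includes a therapy-group random effect on change, either group-by-time or a group effect on post-baseline scores that is zero at T0.
2. State that this effect is kept regardless of AIC or BIC, and limit those criteria to the within-participant covariance.
3. Fit by REML and test condition contrasts with Satterthwaite or Kenward-Roger degrees of freedom that reflect the number of groups (about 26 with 28 groups).
4. Use the same model for the interval compared with the 2.20 margin.

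The cost is wording; no new data are needed. Intervals become slightly wider and a little power is lost if groups do not differ. At 26 df the critical value rises from 1.960 to 2.056, about 5% (2.056/1.960 = 1.05), and the simulated error at ICC 0 was 3.6-3.9%.

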#### Exclusion

Currently in receipt of other evidence-based treatment for depression (psychotherapy or psychopharmacology)Current high risk suicidal ideation or severe self-harming behaviour.Current psychotic episode or severe personality disorder that would interfere with ability to participate in group work.Severe neurological condition or severe learning impairment that would hinder engagement with the content of the proposed interventionsCurrent alcohol or other substance dependence / intoxication

Participants will be monitored throughout the trial for any change in these inclusion and exclusion criteria (e.g., in adjunct treatment status, or in suicide risk). Participants whose mental health declines for any reason will be provided with additional one-on-one supportive counselling by their group facilitator and referred to additional treatment where indicated. If a person who is initially eligible for the trial subsequently meets an exclusion criterion at any point during the active-treatment phase of the trial (T0-T5) they will be excluded from per-protocol analyses, but not intention-to-treat analyses.

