#### Incentives

Participants will not be offered incentives to undertake the intervention, other than receipt of free, evidence-based mental health care. Those participants who are also students enrolled in first-year psychology courses will receive course credit for their participation in the program. To improve attendance at Module 5, where post-program assessments are conducted, all participants will be offered either a coffee or supermarket voucher (AUD$15 value) for attendance. To minimise attrition, participants will be offered AUD$50 incentive to complete each of the 6-month and 12-month follow up assessments. Participants will be followed up unless they actively withdraw from the trial (i.e., data will be sought from participants who did not attend group sessions or who no longer meet inclusion criteria, in order to honour the intention-to-treat principle).

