### Intervention

Participants will be randomly assigned to receive either G4H or CBT. Groups will not commence unless a minimum of 5 people have consented to participate, with the maximum number of people recruited to each group being 9 people. Interventions are matched for contact time and mode of delivery, and both include five group sessions of 60–90 min in duration, run weekly for the first four weeks, and a final “booster” session that is held one month later. Postgraduate students in professional psychology (with provisional registration) will facilitate the groups (2 facilitators per group). Treatment fidelity and consistency of program delivery will be maintained by providing: a half-day of training, weekly group supervision from a registered clinical psychologist, direct observation by investigators to ensure quality, and regular team meetings with the research team. Additionally, G4H facilitators will anonymously complete a brief questionnaire at the end of each session to assess (a) what session activities were covered, (b) the length of session, and (c) facilitator session satisfaction and ease of delivery. Facilitators will also record participant attendance.

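### The two definitions of the per-protocol set conflict, and the one under Analyses makes membership depend on post-randomisation outcome

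*Protocol article*

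**What the plan says.** Under Analyses, the protocol article plans both intention-to-treat and per-protocol analyses for every hypothesis. It describes the per-protocol set as "only including participants who met eligibility criteria throughout the trial period, were randomly assigned, completed the intervention according to the protocol", and also requires baseline and follow-up data.

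Under Exclusion, it says that "Participants will be monitored throughout the trial for any change in these inclusion and exclusion criteria". It then gives a specific rule: a person who was eligible at entry and "subsequently meets an exclusion criterion at any point during the active-treatment phase of the trial (T0-T5) they will be excluded from per-protocol analyses", though not from intention-to-treat analyses. The exclusion criteria include "Current high risk suicidal ideation or severe self-harming behaviour" and receipt of other evidence-based treatment for depression. The same section refers people who decline to additional treatment where indicated.

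Under Inclusion, entry needs one of three things: PHQ-9 of 5 or more, a health-professional diagnosis, or UCLA loneliness of 40 or more. Age 15 to 25 and speaking English also apply. Under Incentives, the article foresees that eligibility can lapse: "data will be sought from participants who did not attend group sessions or who no longer meet inclusion criteria".

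The trial is non-inferiority, with a margin of 2.20 DASS-21 depression points. H2 counts a non-significant condition-by-time interaction, with improvement in both arms, as support.

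**The concern.** The two passages lead to different analysis sets. They differ on which criteria count (exclusion criteria only, or all eligibility criteria) and for how long (T0 to T5, or the whole trial, with follow-up to T7). Two analysts could each follow the article and include different people, and the choice could be made after seeing the data.

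Both rules also condition on what happens after randomisation. The Exclusion rule can remove people who worsen or who start other treatment. The Analyses wording can in addition remove people who get better, because two of the three entry routes are symptom scores. The UCLA scale is a primary outcome, and the PHQ-9 is a second depression measure.

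In a non-inferiority trial the per-protocol analysis is usually read as the check on intention-to-treat. A set selected on outcome is a weak check. Under H2's rule, both a shrunken difference and a smaller set make a non-significant interaction more likely.

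**Working it through.** **The plan's own figure.** Inputs from Sample size power calculations: difference 2.2, SD 4.53, power 0.80, alpha 0.05 (taken as two-sided, or one-sided 0.025). n per arm = 2 × (4.53/2.2)² × (1.960 + 0.842)² = 66.6, so 67. Recruitment: 400 × 0.50 × 0.67 / 2 = 67. Both agree with the article.

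**Who leaves under each rule.**

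- *Exclusion section:* anyone meeting an exclusion criterion from T0 to T5. No listed exclusion criterion is met by improving.
- *Analyses section, read literally:* the same people, those who meet an exclusion criterion after T5, and those who lose every symptom route into the trial. Because the routes are joined by OR, the last group is people with no diagnosis whose PHQ-9 is below 5 and UCLA below 40. Table 1 gives both full scales only at T0, T5, T6 and T7, so this could be seen only from T5 on.

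**Size of the bias.** The documents give neither removal shares nor a correlation, so both are assumptions. Simulation: normal outcome, SD 4.53, G4H truly worse by 2.20 (exactly the margin), 67 per arm before removal, one common removal rule in both arms, acting on a marker with correlation r to the outcome. Clustering by therapy group is ignored. With d the difference among those kept, the upper limit is d + 1.96 × SE and the chance of declaring non-inferiority is Φ((2.20 − d)/SE − 1.96).

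With nobody removed, SE = 4.53 × √(2/67) = 0.783, the upper limit is 2.20 + 1.96 × 0.783 = 3.73, and the chance is 2.5%.

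| Removed | d (r = 0.7) | SE | Upper limit | False non-inferiority | d (r = 0.5) | False non-inferiority (r = 0.5) |
|---|---|---|---|---|---|---|
| Worst 10% | 1.89 | 0.77 | 3.4 | 6% | 2.04 | 3.9% |
| Best 20% | 1.76 | 0.78 | 3.3 | 8% | 1.98 | 4.6% |
| Best 20%, worst 10% | 1.48 | 0.77 | 3.0 | 16% | 1.83 | 6.4% |
| Best 30%, worst 10% | 1.39 | 0.80 | 3.0 | 17% | 1.78 | 6.6% |

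The first row is closest to the Exclusion rule. The others add recovery, as the Analyses wording allows. At zero correlation the difference stays at 2.20.

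**Can it go the other way?** Yes. Assume no true depression difference, a correlation of 0.6 between depression and loneliness, G4H better on loneliness by 0.4 to 0.6 SD (the direction H1 expects), and removal when both scores fall more than 0.3 SD below the CBT mean. About 24% of CBT and 30–33% of G4H are removed, and G4H looks worse by 0.5 to 0.7 points.

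**The case against.** The strongest reply is that the clause under Analyses is shorthand for the rule under Exclusion. That rule is the only one worked out, and it names exclusion criteria only. The remark under Incentives about lapsed inclusion criteria concerns collecting data for intention-to-treat, not removal from per-protocol. Read literally, the clause would also drop anyone who turned 26 during follow-up, which is unlikely to be intended. This makes the broad reading less probable, but it does not remove the conflict: the sentence that defines the set says something else, and the Exclusion section itself monitors inclusion criteria.

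The diagnosis route keeps many recoverers eligible, so the larger removal shares may be too high. That stands. So does the point that intention-to-treat, which keeps these people, is run for every hypothesis. Per-protocol is never the only analysis, although the article does not say how the two combine for H2.

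Removing people who start other depression treatment is a conventional per-protocol choice. Keeping them can itself dilute the contrast, so this is a trade-off and not an error.

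A reader might also infer that poor CBT delivery would go unseen, because "G4H facilitators will anonymously complete a brief questionnaire at the end of each session" and no such form is described for CBT. The article does not support that. Under Intervention, training, supervision, direct observation and attendance records are not limited to one arm, and Table 1 lists the facilitator questionnaire without an arm restriction.

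**Conclusion.** The concern holds as a conflict between two definitions, with a risk of bias. The sections differ on criteria and on time window, and the Analyses wording, followed as written, selects on post-randomisation outcome.

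Under the assumed removal of 10–40%, a true deficit of 2.20 shrinks to about 1.4–1.9 at correlation 0.7, and false non-inferiority rises from 2.5% to about 6–17%. At correlation 0.5 it rises to about 4–6.6%. These figures rest on assumed shares, a common rule in both arms and no clustering.

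Two stronger readings go too far. One is that a deficit at the margin would look safely inside it: the expected upper limits of 3.0 to 3.4 all lie beyond 2.20, so the error rate is inflated but non-inferiority would still usually not be shown. The other is that the arms are bound to be pulled together: that is the typical direction, but greater loneliness recovery under G4H could push them apart.

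**What to change.** Under Analyses, replace the requirement of eligibility over the whole trial period with eligibility criteria met at baseline (T0). Define the rest of the set by exposure to the allocated program, using the same attendance rule in both arms. Then reconcile this with the Exclusion section so that one removal rule and one time window apply throughout.

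If removal for exclusion criteria met during T0–T5 is kept, report the numbers and reasons by arm, and add a sensitivity analysis that retains these people. None of this changes how participants are managed, only who is counted in which analysis.

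The cost is a few sentences of wording and slightly more analysis work.

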The second trial was a Phase II randomised control trial (RCT; [23]) in a sample of adults recruited from the community (*M*_age_ = 31.06; *SD* = 12.80). This RCT examined the efficacy of G4H compared to a Treatment-As-Usual (TAU) control among people with current depression symptoms or health-professional diagnosis of a mental illness (*N* = 120). In this trial, the TAU group received a diverse range of interventions, with more than 50% receiving antidepressant medication, psychotherapy, or both. Intention-to-treat analyses showed that people in the G4H condition experienced a significant decline in loneliness, social anxiety and primary care attendance, and a significant increase in their sense of belonging to multiple groups, relative to TAU. There was also evidence of significant pre-post improvement in depression among those who completed G4H, although this was not significantly greater than the improvement seen in the TAU condition.

These data suggest that G4H has good potential to benefit the mental health of young people in treatment. The next important stage is to test G4H against a *uniform, active treatment.* This is the purpose of the present program of research with young adults with depression.

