## Method

### Trial design

CARR is a two-arm non-inferiority parallel (1:1 ratio) randomised controlled trial. A summary of this study’s compliance with Standard Protocol Items: Recommendations for Interventional Trials (SPIRIT), is provided in the Additional file 1.

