### Recruitment

Allied health professionals and professionals-in-training at the two services will be invited to participate in an information session, which will include selection criteria for the participants, and a flyer for them to display within the service to inform participants of the program. These professionals will identify eligible patients for inclusion into the study on a rolling basis. They will approach potential participants and provide them with contact details for trial staff, including a website with links to the Participant Information Sheet and Consent Form. Research staff will contact potential participants to conduct screening and assessment, explain the study in more detail, answer any questions arising, and go through the consent process. If a potential participant indicates thoughts of self-harm in the baseline measures (i.e., a score of 3 or 4 on item 9 of the PHQ-9), a risk assessment will be conducted at this stage. Participants will provide fully informed, written and voluntary consent. Additionally, for those participants aged 16 or under, their parent or guardian will be informed of their participation and provided with an information sheet with the permission of the young person. However, primacy will be given to the consent of the young person, in line with the organisational policies of the research setting (which does not require parental consent for young people to access mental health services). Participants will be eligible to complete the CARR trial either as an (evidence-based) alternative to standard care, or while they are on a waiting list for standard care.

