#### Group cognitive behaviour therapy

The active comparison condition will involve the delivery of the current best-practice intervention for the treatment of adolescent depression: CBT. Specifically, an existing brief manualised program for group-based CBT for depression [27] will be used with minor adaptations to ensure comparable structure and amount of face-to-face contact as the G4H condition. This specific manualised version of CBT has been found to be effective in reducing depression symptoms in a sample of high-risk adolescents relative to active control groups (*N* = 341; [28]). Indeed, a meta-analysis found that this particular manualised program showed greater effect sizes than similar interventions with longer duration [29].

The manualised program involves the following components: (1) psychoeducation, in which participants learn about the link between thoughts, mood, and behaviour; (2) behavioural activation, in which participants learn strategies to increase activities that boost their sense of pleasure and achievement; and (3) cognitive restructuring, in which participants learn strategies for challenging and reframing unhelpful thinking patterns that maintain depression. The program also includes homework tasks and group-based activities.

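### H2 takes significant pre-post improvement within each arm as evidence of benefit, which a trial with two active arms and no untreated arm cannot supply

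*Protocol article*

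**What the plan says.** All references are to the protocol article.

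- **Trial design:** "CARR is a two-arm non-inferiority parallel (1:1 ratio) randomised controlled trial". Under Group cognitive behaviour therapy, the comparator is itself a treatment: "The active comparison condition will involve the delivery of the current best-practice intervention for the treatment of adolescent depression: CBT". There is no untreated or wait-list arm.
- **Inclusion:** entry is by PHQ-9 of 5 or more, or a diagnosed mental health condition, or UCLA loneliness of 40 or more.
- **Analyses, H2:** "H2 will be considered supported if there is evidence of significant improvements in depression in both conditions", and the rule adds that the condition-by-time interaction must be non-significant. The next sentence gives a non-inferiority margin of 2.20 DASS-21 depression points, but nothing ties that margin to the H2 decision.
- **Analyses, H1:** support requires "evidence of significant improvements in loneliness in the G4H condition (H1a), and a significant condition by time interaction", the second part being H1b.
- **Analyses, H3:** support requires no significant rise in depression or loneliness between T6 and T7 in the G4H arm.
- **Groups 4 health (Background):** G4H completers in the Phase II trial improved significantly in depression, "although this was not significantly greater than the improvement seen in the TAU condition".

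**The concern.** Of the two conditions in the H2 rule, only the within-arm improvement speaks to benefit. A non-significant interaction is also the expected result when neither treatment does anything: at the 5% level it occurs in 95% of such trials.

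The participants are help-seeking young people, many with raised symptom scores, and scores in such samples tend to fall without treatment. Any improvement between T0 and session 1 would also be counted. Recruitment is described as "These professionals will identify eligible patients for inclusion into the study on a rolling basis", and under Intervention "Groups will not commence unless a minimum of 5 people have consented to participate", so some waiting is likely.

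At stake is what a positive H2 means. Under the stated rule, the trial could declare H2 supported, and readers could take both treatments to have worked, when both arms merely followed the course of time. This is separate from the weakness of treating a non-significant interaction as equivalence. If that part were repaired and the within-arm requirement kept, the requirement would still look like a check on efficacy without being one.

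**Working it through.** **Inputs from the article.** SD 4.53, difference 2.2, power 0.80, alpha 0.05, 67 retained per condition, d = 0.49 and 67% retention (Sample size power calculations); margin 2.20 (Analyses); improvement above 3 points as clinically significant (Primary outcomes).

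**Assumptions not in the article.** Pre-post correlation r of 0.5 to 0.7; arms starting k = 0.5 to 1 SD above their long-run mean; a simple paired comparison in place of the planned mixed model; no clustering unless stated.

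**1. The plan's own figure.** n = 2 × (1.96 + 0.84)² × 4.53² / 2.2² = 66.5, so 67 per arm. It reproduces with two-sided 0.05, or equivalently one-sided 0.025; one-sided 0.05 gives 53. Also 200 × 0.67 / 2 = 67, and 0.49 × 4.53 = 2.22.

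**2. Smallest significant fall within one arm.** SD of change = 4.53 × √(2(1 − r)); SE = SD of change / √67; threshold = 1.96 × SE.

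- r = 0.7: SD 3.51, SE 0.429, threshold 0.84 points.
- r = 0.5: SD 4.53, SE 0.553, threshold 1.08 points.

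That is 28-36% of the 3-point change (0.84/3, 1.08/3) and 38-49% of the margin (0.84/2.20, 1.08/2.20).

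**3. Regression to the mean alone, no treatment effect.** Expected fall = (1 − r) × k × 4.53. Chance per arm = Φ(fall/SE − 1.96). The last two columns come from 5,000 simulated trials per row.

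| k | r | Fall | Per arm | Both arms significant | All of H2 met |
|---|---|---|---|---|---|
| 0.5 | 0.7 | 0.68 | 35% | 12% | 12% |
| 0.5 | 0.5 | 1.13 | 53% | 28% | 28% |
| 0.75 | 0.7 | 1.02 | 66% | 42% | 41% |
| 0.75 | 0.5 | 1.70 | 87% | 74% | 72% |
| 1.0 | 0.7 | 1.36 | 89% | 78% | 77% |
| 1.0 | 0.5 | 2.27 | 98% | 96% | 93% |

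A t-based calculation for k = 1, r = 0.7 gives 0.878 per arm, so 0.878² = 77% for both arms.

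**4. Any non-treatment fall, whatever its cause.** Both arms are significant in 19-42% of trials at a mean fall of 1.0 point (0.439² to 0.645²), 60-88% at 1.5 points (0.773² to 0.938²) and 90-99% at 2.0 points (0.951² to 0.997²), for r = 0.5 to 0.7.

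**5. Clustering.** With an assumed design effect of 1.3 for therapy groups, the chance of meeting all of H2 (normal approximation, r = 0.7 to 0.5) is 60-85% at k = 1 and 8-18% at k = 0.5.

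**6. A between-arm rule.** With SD 4.53 and 67 per arm, the 95% interval for the difference has half-width 1.96 × 4.53 × √(2/67) = 1.53 points, inside the 2.20 margin when the arms are equal.

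**The case against.** **Within-arm improvement is never sufficient by itself.** This stands for H1: H1a is joined by *and* to a significant interaction, so it can only make H1 harder to declare. H3 contains no test of improvement. A reader might infer that all three hypotheses share the fault; the decision rules do not support that.

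**The protocol has other evidence that CBT works.** This also stands. The article cites a trial of this CBT manual against active controls (N = 341) and an effect of d = 0.49 against control. Resting on historical comparator evidence is normal in a two-arm non-inferiority trial, and the missing third arm belongs to the design. But the H2 rule does not invoke that evidence; it invokes within-arm significance. Whether the evidence and the margin built on it are adequate is a separate question.

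**A confidence limit cannot separate two effective from two ineffective treatments either.** Correct. The change does not create an internal efficacy check. It removes one that only appears to work and ties the decision to the margin.

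**The stronger claim that time alone would usually satisfy H2 is not shown.** A reader might infer it from the 1 SD rows. The article gives no DASS-21 baseline excess; its only mention of 1 SD concerns the UCLA loneliness cut-off. Entry is by PHQ-9 in the mild range, UCLA or a diagnosis, not by DASS-21, so step 3 overstates regression on that scale. At 0.5 SD both arms pass in only 12-28% of trials.

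**Phase II does not show what an untreated arm would do.** More than half of its treatment-as-usual arm received medication, psychotherapy or both, and the sample's mean age was 31.06. The result shows that significant pre-post change can occur without a demonstrated advantage over a comparator. It says nothing about time alone, and that arm is unsuitable as a benchmark for people aged 15 to 25 who are not receiving other evidence-based depression treatment.

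**The wait before session 1 is partly inferred.** Recruitment suggests that baseline measures accompany screening, but Measures says only that T0 precedes the intervention. No interval is given, and the full protocol may fix one.

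**Conclusion.** The point holds for H2. The rule in Analyses makes significant improvement within both arms a condition of support, and with two active arms that condition cannot show that either treatment worked. The threshold is low: about 0.8 to 1.1 DASS-21 points at 67 per arm, SD 4.53 and r of 0.7 to 0.5, a change that natural recovery or regression to the mean could produce.

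The chance that both arms pass with no treatment effect is uncertain: about 12-28% at a baseline excess of 0.5 SD and about 77-96% at 1 SD. Clustering and entry on other scales lower it; natural recovery on top of regression raises it. The conclusion does not need any particular value in that range, because within-arm significance cannot identify the cause of the fall.

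The weakness changes what a positive H2 can be said to mean. It does not undermine H1, which H1b protects, and it does not touch H3.

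**What to change.** In Analyses:

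1. Decide H2 on the confidence limit for the between-arm difference in DASS-21 depression change (G4H minus CBT, higher scores worse). H2 is supported if the upper limit is below 2.20. A two-sided 95% interval, from the mixed model with its therapy-group level, matches the stated 67 per arm.
2. Decide H1 on H1b.
3. Report within-arm changes descriptively. State that they do not show effectiveness because no arm is untreated, and that any inference that both treatments work rests on the historical CBT evidence cited under Group cognitive behaviour therapy and Sample size power calculations.
4. Do not use the Phase II treatment-as-usual arm as a benchmark.

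Optional: if the full protocol does not already do so, take or repeat the brief depression and 4-item loneliness page shortly before each group is randomised, so that change during the wait is not counted.

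The cost is a rewording of the decision rules and at most one extra page per participant. The downside is a narrower conclusion: H2 would show only that G4H is not worse than CBT by more than the margin.
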